# Effects of physical training on functional, clinical, morphological, behavioural and psychosocial outcomes in post-COVID-19 infection: COVID-19 and REhabilitation study (CORE-study)—a study protocol for a randomised controlled clinical trial

**DOI:** 10.1186/s13063-022-07055-5

**Published:** 2023-01-19

**Keywords:** COVID-19, Rehabilitation, Physical training, Multicomponent exercise

## Abstract

**Background:**

The COVID-19 pandemic remains ongoing, with a significant number of survivors who have experienced moderate to severe clinical conditions and who have suffered losses of great magnitude, especially in functional capacity, triggering limitations to daily autonomy and quality of life. Among the possibilities of intervention for disease rehabilitation, physical exercise training stands out, which can benefit several health outcomes and favours the adoption of healthier behaviours. Therefore, the aim of the study will be to analyse the effects of physical training on the functional, clinical, morphological, behavioural and psychosocial status in adults and the elderly following COVID-19 infection.

**Methods:**

A randomised controlled clinical trial is to be conducted in parallel, with the experimental group undergoing an intervention involving a multicomponent physical rehabilitation programme, carried out at the Sports Center in partnership with the Academic Hospital of the Federal University of Santa Catarina, in Florianópolis, Brazil. Participants will be adults and the elderly, of both sexes, in a post-COVID-19-infection state, who were hospitalised during the infection. The intervention will have a total duration of 24 weeks and will include a multicomponent physical training programme, which will have gradual progression in frequency, duration and intensity over time. Regarding the outcomes, before, at the 12th and after 24 weeks of intervention, functional (primary outcome = functional index of aerobic capacity), clinical, morphological, behavioural and psychosocial outcomes will be assessed.

**Discussion:**

This study will contribute to a greater understanding of the safety, adherence and benefits of physical training in the rehabilitation of post-COVID-19 patients. The results of this study will be disseminated through presentations at congresses, workshops, peer-reviewed publications and local and international conferences, especially with a view to proposing a post-COVID-19 rehabilitation care protocol.

**Trial registration:**

ReBEC, RBR-10y6jhrs. Registered on 22 February 2022. 2015.

**Supplementary Information:**

The online version contains supplementary material available at 10.1186/s13063-022-07055-5.

## Introduction

Among the various viruses that cause upper airway infections, influenza A, rhinovirus and coronavirus stand out, being present in more than 70% of cases of respiratory infections, which makes it necessary for greater knowledge and effective therapy against these diseases. Respiratory infections of viral etiology are considered a public health problem, causing a high and constant increase in mortality rates worldwide [1]. These diseases are highly communicable and pose a risk to the population, even though they are linked to the environment and are more preventable than diseases in other organ systems [1]. Outbreaks, such as those of severe acute respiratory diseases (SARD) already existing in human history, show that there are environmental and individual factors that people can adopt to protect themselves and others [2].

More than one million people became ill with the H1N1 flu between April and June 2009 in the USA, with cases with complications, with the development of severe pneumonitis and SARD and with consequent multiple organ failure. Three months after hospital discharge for SARD, up to 80% of patients demonstrated reduced diffusion capacity as well as reduced quality of life [3].

In this condition, post-H1N1 with complications [4] found improvements in pulmonary function, functional capacity and quality of life after 2 months of a multicomponent training (resistance, respiratory and aerobic) in patients previously hospitalised. However, in January 2020, something completely new emerged, which the World Health Organization (WHO) declared a public health emergency: the disease caused by the novel coronavirus (COVID-19). In March of that year, it was characterised as a pandemic, with significant global impacts, especially on health and the economy [5, 6]. The disease known as COVID-19 is characterised by a viral infection caused by the type 2 coronavirus (SARS-CoV-2), providing a varied and complex clinical scenario, with likely impairment in several organ systems, which can present from mild to moderate signs and symptoms up to a picture of severe acute respiratory syndrome [5, 7].

The possible clinical manifestations in patients with COVID-19 are wide and include fever, cough, breath shortness, dyspnea, appetite loss, nausea, vomiting, diarrhoea, muscle pain, general fatigue, headache, smell or taste dysfunction and mental confusion. Furthermore, the disease can progress to more serious complications, including severe acute respiratory syndrome (SARS), acute kidney injury, anaemia, heart failure and secondary infection [8].

In Brazil, as occurred in different regions of the world, the health organisations, especially the public system, were largely affected by the COVID-19 pandemic. The fight against this pandemic condition basically takes place in three types of action: (a) the prevention of contagion throughout the promotion of preventive actions, such as social distancing, use of masks, adequate hand hygiene and immunisation strategies in the national territory [5]; (b) treatment of patients during the viral cycle through therapies according to the level of impairment, aiming to reduce the chance of sequelae and, above all, mortality [9]; (c) rehabilitation of patients after the viral cycle, aiming at the recovery of the different organic systems affected to reintegrate people with autonomy and quality of life into society [8].

The current scenario demonstrates that the number of survivors is highly expressive, especially those who experienced moderate to severe clinical conditions in the acute phase of the disease, who suffered losses of great magnitude, especially in functional capacity, limiting autonomy and quality of life. In this context, the literature has presented a clinical picture in which people manifest continuous symptoms after their initial COVID-19 infection, called “long COVID” or “post-COVID syndrome”. This syndrome is a multisystem condition with a number of debilitating symptoms, including fatigue, dyspnea, cough, chest pain, headache, muscle pain and gastrointestinal problems, among others. In addition, people with “long COVID” can experience psychological and cognitive problems, such as depression, anxiety and post-traumatic stress disorder. These symptoms can result in significant impacts on the subject’s ability to perform their daily and even work tasks [10–12].

Given this varied profile of persistent symptoms chronically impacting people’s lives, interventions are necessary that at least minimise the negative impact of the disease, especially on functional capacity. For this, the need for research into the role of physical exercise in the rehabilitation of patients, given the great number of benefits of exercise in the rehabilitation of other frail populations, is understandable. In post-COVID rehabilitation, a review by Sun et al. [8] demonstrated benefits such as improved patient awareness, reduced mechanical ventilation time, improved respiratory function and reduced risk of complications, mortality rates and risks of readmission. Furthermore, according to the authors, in the case of patients who have COVID-19 in whom it is manifesting in a severe and critically ill manner, rehabilitation should only begin when the patient’s condition is stable. Among the exercises proposed for rehabilitation in the studies that made up the review, there are respiratory exercises, postural maintenance and control, active and passive joint mobility, standing and standing independently. Still, some studies have reported benefits of conventional [13] and unconventional exercise models [14] in post-COVID patients.

Although the number of scientific investigations on the topic of post-COVID rehabilitation has been growing, to date, few studies have precisely investigated the effects of physical rehabilitation in patients who have had moderate to severe COVID-19. Furthermore, the recent literature on physical training in post-COVID-19 rehabilitation is still lacking in terms of multicomponent protocols (a combination of two or more components, such as aerobic, resistance, balance and flexibility exercises in the same training session) in a progressive approach to the variables (volume and intensity) of training. A multicomponent approach is important due to multisystemic losses found in this population. In this direction, it is important to intervene in the main physical capacities impacted by the disease and associated with functional losses. Multicomponent training has been shown to be the most beneficial type of exercise to improve the functional capacity of frail older people [15–17]. Also, as the post-COVID-19 condition is still not completely understood, presenting a certain heterogeneity among patients to provide training for multiple physical capacities is more prudent than a more specific approach regarding the type of training.

Thus, the objective of this study is to describe the methodology used in a randomised clinical trial that seeks to analyse the effects of a rehabilitation programme on clinical, functional, morphological, behavioural and psychosocial outcomes in patients who were infected with SARS-Cov-2.

## Methods

### Design

This is a randomised controlled trial (RCT), of superiority and unicentric, conducted in parallel with blinding of outcome assessors. The study will have two arms: a multicomponent physical training arm, with progression in volume and intensity, and a control arm, without structured exercise. The study is registered in the Brazilian Registry of Clinical Trials (code RBR-10y6jhrs).

### Setting

All procedures of this study will be performed at the Federal University of Santa Catarina (UFSC), located in Brazil. Recruitment and eligibility, as well as the assessment of several outcomes, will take place at the Asthma and Airway Inflammation Research Centre (NUPAIVA) at the University Hospital at UFSC facilities. The rehabilitation programme (intervention) and the evaluation of other outcomes will be carried in the facilities at the sports centre UFSC. Among these facilities, there are three other places for the exercise intervention, namely the rehabilitation centre, the strength training room and the athletics track and field, all located at UFSC.

### Participants

The whole sample (including men and women > 18 years old) who were hospitalised for the treatment of COVID-19 and who experienced moderate or critical conditions in the acute phase of infection, will participate in this study.

Patients who have been discharged from hospital for at least 6 weeks and who meet the following criteria will be included: 72 h afebrile without the use of antipyretics and stabilisation of respiratory symptoms; absence of mechanical ventilation and tracheostomy devices; absence of hypersecretion with ineffective cough; absence of severe dyspnea, difficult to stabilise, at rest and in activities of daily living; respiratory rate < 18 breaths per minute; peripheral O_2_ saturation (SpO_2_) > 90%; normal resting electrocardiogram (12-lead); control of underlying diseases (under medical supervision); absence of open lesions; ability to sit and stand without assistance; ability to maintain balance in the standing position; and a stable level of consciousness and absence of mental confusion. Besides that, at the beginning of the research, patients will not be able to engage in exercise programmes with a focus on aerobic, resistance or balance components, at a frequency of twice a week or more.

The selection of participants will occur on a voluntary and non-probabilistic basis. Participants will be recruited from a list of patients who had treatment at the University Hospital and will be provided by the NUPAIVA team of physicians and physiotherapists. From this list, the research team of kinesiology professionals will invite the potential participants via phone call or messaging app.

If sample *n* is not reached, media dissemination will be carried out, aiming to reach patients who were hospitalised in other hospitals. Also, if the sample *n* is not reached only with hospitalised patients, the recruitment will be open to patients who, after infection by COVID-19, present chronic fatigue, moderate to severe, as evaluated by the Chalder scale [18].

All eligible patients interested in participating in the current study will undergo a medical screening, consisting of clinical evaluation and ECG analysis. Once the patients are allowed to exercise, the research team will schedule a meeting to explain the study procedures and for the signing of the informed consent form. For those who consent to participate, a complementary anamnesis will be applied to the medical screening, with a primary focus on lifestyle, and later the battery of tests for baseline assessment will be scheduled (Fig. 1).

**Fig. 1 Fig1:**
[figure not shown]
Schedule of enrolment, interventions and assessments

### Sample size calculation

The sample size calculation was based in an RCT [19] with a population and design similar to the present study. The calculation was performed for the distance covered in the 6-min walk test, the primary exercise outcome of the present study. This aforementioned study showed within-group and between-group changes (i.e. improvement of 50 m on the distance covered) after intervention in favour of the experimental group, which would be expected in the present study. The calculation was performed using the G*POWER 3.1 programme, adopting a significance level of 0.05, a power of 80% and a correlation coefficient of 0.5. The resulting *n* is 22 participants in each group. Considering a likely sample loss of around 30%, the recruitment will aim to reach an *n* sample of 30 participants for each group, totalling around 60 participants. The expected flow of participants into the trial is six to eight participants (blocks) every 15–25 days.

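### Thirty per group is slightly too few for the plan's own 30% loss: 21 remain where 22 are required, and power falls from 80% to about 78%

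*Protocol article*

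**What the plan says.** All the figures are in the Protocol article under Sample size calculation. The basis is a cited trial: "The sample size calculation was based in an RCT [19] with a population and design similar to the present study". The effect is described as "within-group and between-group changes (i.e. improvement of 50 m on the distance covered"), in favour of the experimental arm. The calculation was done in G*Power, "adopting a significance level of 0.05, a power of 80% and a correlation coefficient of 0.5". The resulting n "is 22 participants in each group". The allowance for loss follows: "Considering a likely sample loss of around 30%, the recruitment will aim to reach an" n of 30 per group, or around 60 in total.

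Four other sections bear on the point:

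- **Primary outcomes** defines the endpoint as six-minute walk distance after 24 weeks.
- **Functional capacity** adds a walk test at week 12.
- **Analysis plan** specifies generalised estimating equations, an intention-to-treat analysis on all available data with multiple imputation, and a per-protocol analysis.
- **Trial status** reports that the last block was recruited in October 2022.

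**The concern.** The paragraph sets a requirement, a loss rate and a recruitment target, and the three do not agree. An allowance for loss is meant to leave the required number after the loss has occurred. At the stated rate, 30 per group does not do that. What is at stake is how accurately the power is stated: a reader of a null result would take 80% as the power at the loss the plan itself expects.

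The origin of the 22 is also hard to follow. The 50 m is attached to within-group and between-group changes together, and neither an SD nor a test is named. That limits what can be checked. It is not itself evidence of an error.

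**Working it through.** **Inputs, all from Sample size calculation:** required n = 22 per group; loss about 30%; target 30 per group; alpha 0.05; power 80%; correlation 0.5; effect 50 m. Sidedness, SD and test are not stated. A two-sided test is assumed below unless noted.

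**1. The plan's 22.** It cannot be computed forwards without an SD or a standardised effect. It can only be solved backwards, for the SD at which 22 per group gives 80% power to detect a 50 m between-group difference:

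| Test assumed | Implied SD |
|---|---|
| Two-sided two-sample t (d = 0.8646; 50/0.8646) | 57.8 m |
| Arm-by-time interaction, two visits, correlation 0.5 (f = 0.216; 12.5/f) | 57.8 m |
| Two-sided normal approximation | 59.2 m |
| One-sided two-sample t | 65.6 m |
| Baseline-adjusted comparison, correlation 0.5 (57.8/√(1 − 0.5²)) | 66.8 m |

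So 22 is compatible with an SD anywhere from about 58 to 67 m, depending on the test. The article does not say which applies.

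**2. The plan's 30.**

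- Dividing by the share retained: 22/(1 − 0.30) = 31.4, so 32 per group and 64 in total.
- Adding 30% to the requirement: 22 × 1.3 = 28.6, so 29 per group. Thirty is close to this, but the article does not say how it reached 30.
- What 30 per group leaves at 30% loss: 30 × 0.70 = 21.
- The largest loss at which 22 remain: 1 − 22/30 = 0.267, or 26.7%.

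**3. Cost in power.** Fix the standardised effect at the value for which 22 per group gives exactly 80% (two-sided t, d = 0.8646). The noncentrality is d√(n/2).

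- n = 22: 0.8646 × √11 = 2.868 on 42 degrees of freedom, power 80.0%.
- n = 21: 0.8646 × √10.5 = 2.802 on 40 degrees of freedom, power 78.1%.

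The two-visit interaction test at correlation 0.5 also gives 78.1% with 42 participants in total, and the three-visit version gives 77.9%. The loss of about two percentage points therefore does not depend on the unknown SD, and it hardly changes with the test.

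**The case against.** The strongest reply is that the shortfall is immaterial. The loss is worded as around 30% and the total as around 60, and 26.7% is not far from 30%. One participant per group and two points of power would change no design decision, and recruitment is over. This stands as a limit on the size of the point. It does not make the paragraph correct: at the rate the plan states, its target falls below its requirement.

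A second reply is that lost participants are not wholly lost. The intention-to-treat analysis uses all available data and imputes the rest, everyone is invited to the final assessment whatever their adherence, and the walk test is repeated at week 12. This also stands. A comparison of 21 completers per group is a conservative bound on what the planned analysis would deliver. Imputation does not, however, restore the full information of an observed 24-week distance.

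Two stronger readings are tempting, and the document supports neither:

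- **That 80% power holds only if the SD is about 58 m.** That figure belongs to a two-sided t test or a change-score test. Baseline adjustment at the plan's own correlation allows about 67 m, and a one-sided test about 66 m.
- **That the 22 came from a paired within-group test.** The joint mention of within-group and between-group changes, together with "a correlation coefficient of 0.5", might suggest this. A paired test at n = 22 implies an SD of change of about 80 m, and between-group power would then be 53%. But the article gives n for each group and cites a between-group result, and a correlation is an ordinary input to a repeated-measures comparison of arms. The paired route is conjecture.

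**Conclusion.** The point holds in a limited form. The target is under-inflated by two per group (30 against 32; 60 against 64 in total). At exactly 30% loss, 21 per group remain against the 22 required, and power is about 78% instead of 80%. This takes the 22 as correct for 80% power and counts completers only, in a two-sided comparison. It needs no assumption about the SD.

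A reader might go further and conclude that the 80% is unsupported or that true power is far lower. The document does not show that. The SD and test are absent from a condensed article and may be in the cited trial or the full protocol. No SD in the text conflicts with the 22. The 80% cannot be reproduced from the article, which is different from being wrong.

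**What to change.** Enrol no more patients. Replace the loss sentence with wording to this effect: *30 per group retain 22 if loss is at most 26.7%; at 30% loss 21 remain and power is about 78% under the same assumptions.* In the same place, state that the 50 m is the between-group difference, and name the test (with its sidedness) and the SD that gave 22, so that a reader can reproduce the figure.

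The cost is one or two sentences. Conduct, analysis and enrolment do not change. The stated power becomes slightly less favourable.

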### Intervention

The intervention will last 24 weeks and will consist of two weekly training sessions in the first 11 weeks, reassessments in the 12th week and three weekly sessions from the 13th to 24th weeks. The planned training will have two major stages, the first consisting of two mesocycles, with progression primarily in volume, and the second consisting of three mesocycles, with progression primarily in the intensity (Table 1).

**Table 1 Tab1:** Structuring of training sessions throughout the Rehabilitation Program (CORE-Study)

**Weeks**	**Structure (Component-type, volume, intensity, progression)**
1	Familiarisation with the training model (focus on learning movements and perceived effort)
2 a 6	**Balance**—3 exercises performed in three sets of 10–30 s, with evolution in time (10 to 30 s) and complexity (stages). Unipedal balance—standing on one foot, balance transitioning from dorsiflexion to plantar flexion, and getting up from a chair and walking in a straight line. The stages are (1) Support from both hands (chair/instructor/wall); (2) One-handed assistance (chair/instructor/wall); (3) No assistance; (4) With eyes closed. **Aerobic (treadmill walking)**—total: 25 min accumulating 15 min of light intensity (RPE: 12/13) and 9–10 min of passive recovery). Duration of blocks in two levels—5 repetitions of 3-min walk with 2-min passive intervals, or 3 repetitions of 5-min walk with 3-min passive intervals. **Resistance (body weight and rubber band)**—Stretch bench press, Sit and Stand, Neutral Rubber Row, Step Up and Down Step and Plantar Flexion (2 sets of 10 to 15 reps at RPE 12/13, interval of 1 min).
7 a 11	**Balance**—3 exercises performed in three sets of 10–30 s, with evolution of time (10 to 30 s) and complexity (stages). Unipedal balance—standing on one foot, balance transitioning from dorsiflexion to plantar flexion, and getting up from a chair and walking in a straight line. The stages are (1) Support from both hands (chair/instructor/wall); (2) One-handed assistance (chair/instructor/wall); (3) No assistance; (4) With eyes closed. **Aerobic (Treadmill walking)**—total: 25 min (20 min at light intensity (RPE: 12/13) interspersed with 5 min of passive recovery). Duration of blocks in two levels—5 blocks of 4 min of walking with passive 2-min intervals, or 4 blocks of 5-min walking with 2-min passive intervals. **Resistance (body weight and rubber band)**—Stretch bench press, Sit and Lift, Neutral Rubber Row, Step Up and Down Step and Plantar Flexion (3 sets of 10 to 15 reps at RPE 12/13, interval 1 min)—same setting from above.
12	Reassessments of the outcomes from Functional Capacity, Anthropometry and Body Composition, Cardiovascular Parameters and Psychosocial Parameters.
13 a 16	**Aerobic (Walking—treadmill or athletic track*)**—Continuous training—25 min at moderate intensity (RPE: 12/13). **Resistance (machines and free weights)**—Horizontal Leg Press, Sitting Row, Flexion Chair Knee Flexion, Vertical Peck Deck, Plantar Flexion with Back Barbell (3 sets of 12 to 15 RM, 1 min interval)
17 a 20	**Aerobic** (Walking - treadmill or athletic track*)—Interval training—5 repetitions of 5 min (1 min at RPE 15 with 4 min at RPE 12/13). **Resistance (machines and free weights)—**Horizontal Leg Press, Seated Row, Flexion Chair Knee Flexion, Vertical Peck Deck, Plantar Flexion with Barbell on the Back (3 sets of 10 to 12 RM, 1 min interval).
21 a 24	**Aerobic (Walking—treadmill or athletic track*)—**Interval training—6 repetitions of 4 min (1 min at RPE 15 with 3 min at RPE 12/13). **Resistance (machines and free weights)—**Horizontal Leg Press, Seated Row, Flexion Chair Knee Flexion, Vertical Peck Deck, Plantar Flexion with Back Barbell (3 sets of 8 to 10 RM, 1 min interval)

*RPE* rate of perceived effort, *reps* repetitions, *MR* maximum repetitions

*Dependent on climatic factors and the clinical condition of the patients

In stage 1, the sessions will be held at the rehabilitation centre, with a session duration of approximately 60 min, consisting of a joint warm-up (5 min) followed by a balance section (10 min), aerobic training section (25 min), resistance training (15 min) and final stretching (5 min). The order of the main parts (aerobic and resistance) will be alternated over the weeks to reduce their monotony and not prioritise one of the components, in view of the concurrent interference effect that these types of training can exert on each other.

In stage 2, some aerobic training sessions can be performed on the athletics track, depending on the weather conditions, desire and clinical condition of the participants, while the resistance training part will take place in the university gym room.

Three instructors with prior experience with exercise prescription will supervise all the sessions. The programme will also have two physical education students, who will assist in the general procedures of the intervention, from the reception of participants and maintenance of adequate sanitary conditions to specific assistance for the sessions that teachers may need. The performance of a concomitant structured exercise training intervention is prohibited during the trial, except physiotherapy intervention of short duration, which is permitted Fig. 2.

